# Add-on treatment with *N*-acetylcysteine for bipolar depression: a 24-week randomized double-blind parallel group placebo-controlled multicentre trial (NACOS-study protocol)

**DOI:** 10.1186/s40345-018-0117-9

**Published:** 2018-04-05

**Keywords:** Bipolar disorder, Depression, Acetylcysteine, Oxidative stress, Inflammation, Urine, Blood, Treatment, Psychiatry, Genetics

## Abstract

**Background:**

Oxidative stress and inflammation may be involved in the development and progression of mood disorders, including bipolar disorder. Currently, there is a scarcity of useful treatment options for bipolar depressive episodes, especially compared with the efficacy of treatment for acute mania. *N*-Acetylcysteine (NAC) has been explored for psychiatric disorders for some time given its antioxidant and anti-inflammatory properties. The current trial aims at testing the clinical effects of adjunctive NAC treatment (compared to placebo) for bipolar depression. We will also explore the biological effects of NAC in this context. We hypothesize that adjunctive NAC treatment will reduce symptoms of depression, which will be reflected by changes in selected markers of oxidative stress.

**Methods and analysis:**

In the study, we will include adults diagnosed with bipolar disorder, in a currently depressive episode. Participants will undertake a 20-week, adjunctive, randomized, double-blinded, parallel group placebo-controlled trial comparing 3 grams of adjunctive NAC daily with placebo. The primary outcome is the mean change over time from baseline to end of study on the Montgomery–Asberg Depression Rating Scale (MADRS). Among the secondary outcomes are mean changes from baseline to end of study on the Bech-Rafaelsen Melancholia Scale (MES), the Young Mania Rating Scale (YMRS), the WHO-Five Well-being Index (WHO-5), the Global Assessment of Functioning scale (GAF-F), the Global Assessment of Symptoms scale (GAF-S) and the Clinical Global Impression-Severity scale (CGI-S). The potential effects on oxidative stress by NAC treatment will be measured through urine and blood samples. DNA will be examined for potential polymorphisms related to oxidative defences.

*Trial registration*: Registered at The European Clinical Trials Database, ClinicalTrials.gov: NCT02294591 and The Danish Data Protection Agency: 2008-58-0035.

## Background

Bipolar disorder is generally characterized by recurrent episodes of mania (or hypomania) and major depression (Goodwin and Jamison 2007), with depressive phases being the dominant phase in terms of overall duration (Judd and Akiskal 2003).

In recent treatment guidelines for bipolar disorder, combinations of pharmacotherapy and psychotherapeutical treatments such as psychoeducation and individual or group-based psychotherapy are generally recommended (Fountoulakis et al. 2017). Regarding pharmacotherapy, combined use of various drugs is often beneficial in terms of both acute treatment response and for maintenance (Geddes et al. 2016). However, despite all efforts, treatment outcome is often inadequate, necessitating the development of new, more effective treatments. There a scarcity of effective treatments for the acute treatment of bipolar depression, in particular (Grunze et al. 2010).

Studies have indicated that oxidative stress and neuroinflammation seem to be linked to the pathophysiology of bipolar disorder (Andreazza et al. 2008; Berk et al. 2011). Recent studies have reported increased levels of oxidative stress markers in blood and urine samples from patients suffering from bipolar disorder (Andreazza et al. 2007, 2008; Munkholm et al. 2015; Jacoby et al. 2016). Furthermore, there is evidence that the level of oxidative stress may be a state marker in bipolar disorder (Munkholm et al. 2015; Fernandes et al. 2011; Polyakova et al. 2015).

The brain is thought to be especially vulnerable to oxidative stress due to its’ high metabolic demands and its’ limited capacity of defences such as glutathione (GSH), which is the central antioxidant in all tissues (Ballatori et al. 2009). Bipolar disorder is associated with decreased GSH levels, resulting in increased oxidative stress (Andreazza et al. 2008; Rosa et al. 2014; Brown et al. 2014; Soeiro-de-Souza et al. 2013). *N*-Acetylcysteine (NAC), the acetyl derivative of the amino acid cysteine, improves the l-cysteine supply, which increases GSH levels in the brain (Choy et al. 2010; Dean et al. 2009). Accordingly, NAC treatment appears to decrease oxidative stress and inflammation (Dean et al. 2011). Two previous clinical trials on NAC for bipolar disorder have shown significant effects on depressive symptoms (Berk et al. 2008, 2011).

### Study rationale

Given the paucity of effective pharmacotherapy for bipolar depression, it seems warranted to test whether the previous positive findings of NAC for bipolar depression can be replicated in a Danish study sample. Furthermore, we wanted to go further than these studies by exploring the antioxidant effects of NAC in the context of the clinical trial. Finally, it would be useful for the development of new pharmacotherapies in general to test whether the potential antidepressant efficacy of NAC is linked to its antioxidant effects. In addition to the latter point, finding a relationship between the level of oxidative stress at baseline and the efficacy of NAC would be a step towards the goal of precision psychiatry (Fernandes et al. 2017).

### Aims and objectives

The primary aim is to investigate the effects of adjunctive NAC treatment on depressive symptoms in participants diagnosed with bipolar depression. The secondary aims are to measure the biological effect of NAC treatment based on markers of oxidative stress in urine samples.

The study objectives are following:

#### Process aim 1

Assessing baseline adjusted between-group mean change between NAC and placebo group from baseline up till week 20 on The Montgomery–Asberg Depression Rating Scale score (MADRS) (Montgomery and Åsberg 1979).

#### Process aim 2

Assessing baseline adjusted between-group mean difference between NAC and placebo group from baseline up till week 20 on; the Bech-Rafaelsen Melancholia Scale (MES) (Bech 2002), the Young Mania Rating Scale (YMRS) (Young et al. 1978), the WHO-Five Well-being Index (WHO-5) (Staehr 1998), the Global Assessment of Functioning scale (GAF-F), The Global Assessment of Symptoms scale (GAF-S) (Jones et al. 1995) and the Clinical Global Impression-Severity scale (CGI-S) (Guy WNIoMHPRBECDEP 1976).

#### Process aim 3

Assessing baseline adjusted between-group mean difference between NAC and placebo group from baseline up till week 20 in urine samples to explore biological correlation in DNA and RNA damage by oxidative stress.

#### Process aim 4

Assessing baseline adjusted between-group mean difference between NAC and placebo group from baseline up till week 24 on MADRS, MES, YMRS, WHO-5, GAF-F, GAF-S, CGI-S and urinary markers.

#### Process aim 5

Assessing baseline urinary markers to explore correlation in DNA and RNA damage by oxidative stress and the degree of depression severity.

Additionally, blood samples and DNA are collected for further explorations towards detecting potential genetic polymorphisms related to oxidative defences, but are currently stored.

## Methods

### Trial design

This is a 20-week randomized, double-blind, parallel group, placebo-controlled, multicentre trial, with a 4-weeks follow up after study treatment discontinuation. The protocol is developed in accordance with the Standard Protocol Items: Recommendations for Intervention Trials (SPIRIT) 2013 Guidelines (Chan et al. 2013). The study will follow the Consolidated Standards of Reporting Trials (CONSORT) guidelines to describe, report and publish the results (Schulz et al. 2010).

### Visits and telephone calls

The study visits (outlined in Fig. 1) are planned to be at week 2, 10, 20 and 24 (± 7 days for each visit). Furthermore, participants will be contacted via telephone 6 and 15 weeks after inclusion (± 7 days). Telephone calls are conducted with participants to support adherence and provide an opportunity for participants to discuss any issues with the study (including adverse events).

**Fig. 1 Fig1:**
[figure not shown]
Timeline with outcomes measures. *M.I.N.I-interview* Mini International Neuropsychiatric Interview, *MADRS* Montgomery–Asberg Depression Rating Scale

### Participant selection

The study participants will be recruited amongst in-and out patients from the Mental Health Services from three study centres covering three geographical areas (three cities in centre one and two, and one city in centre three). We plan to recruit participants over a study period of 2 years.

Participants assess for eligibility will be screened according to the inclusion and exclusion criteria.

### Participant eligibility

#### Inclusion criteria

Participants will be included if they meet all of the following criteria:18–64 years of age at baseline (inclusive).A diagnosis of bipolar disorder type I or II, current episode of depression according to Diagnostic and Statistical Manual of Mental Disorders 5 (DSM-V) (American Psychiatric Association 2000) (evaluated by using the M.I.N.I (International Neuropsychiatric Interview), version 5.0 in Danish (Sheehan et al. 1998).At least one documented affective episode within the last 6 months within the index period (depressive, manic or mixed), as judged by the principal investigator (according to the medical journal, and clinical interview based on the M.I.N.IHave had symptoms of depression for at least 4 weeks up till screening, and a Montgomery–Asberg Depression Rating Scale (MADRS) score of ≥ 18 (mild depression or more) at that time.Have given full oral and written informed consent.

Female participants should present a negative pregnant test at baseline and will be informed to use effective contraception throughout the study period.

#### Exclusion criteria

Participants will be excluded if they meet any of the following criteria:Have a daily intake of more than 500 mg NAC, 200 μM selenium, or 500 IU of vitamin E at screening.Have received electroconvulsive therapy (ECT) within the last 4 weeks prior to screening.Have epilepsy, chronic asthma or allergy towards NAC, as judged by investigator.Involuntary admitted, detainment or treated according to the statutes defined in the Mental Health Act.Cannot speak or understand the Danish language.Females planning pregnancy or breastfeeding during the timeframe of the study.

#### Discontinuation criteria

Participants will discontinue the study under the following circumstances:Withdrawal of consent.Discontinues study treatment for 7 or more consecutive days.Does not comply with the defined study visits (visits within 7 days prior or after the computer-generated date).Becomes pregnant, initiates breastfeeding, or wishes to become pregnant during the study period.Becomes hypersensitive to histamine, as judged by investigator.Develops serious adverse reaction/event (SAR/SAE) i.e. suspected to be associated with the study treatment, as judged by an investigator.Stops using effective contraception.Changes diagnosis during the study, and the primary diagnosis is no longer bipolar affective disorder.Involuntary admitted, detainment or treated according to the statutes defined in the Mental Health Act.Becomes increasingly suicidal during the study as judged by investigator.

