### Serious adverse reactions/events and adverse reactions/events

SARs, SAEs, Adverse Events (AE) and Adverse Reactions (AR) are defined according to good clinical practice (GCP), and assessed at each visit. Participants who discontinue study participation due to SAEs or SARs will be followed until the SAE/SAR has disappeared or the SAE/SAR is stable. Participants will be contacted with a few days after SAE/SAR and again after 4 weeks.

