### Statistical analysis plan

A statistical significant difference in mean change on MADRS-score, between study groups, from baseline to end of study, is the primary outcome measure of the study. The remaining clinical and biological measures are secondary outcome measures and will be analysed using the same approach as the primary outcome. To investigate the difference in response and remission rates between study treatments at week 20 and 24, logistic regression models will be applied to estimate the odds ratios. The definition of a “responder” is a person which symptoms of depression has dropped 50% in MADRS-score from baseline to week 20 or 24, and “remitters” are defined as MADRS score < 10 (Hawley et al. 2002) at week 20 or 24. Data analysis will be conducted by the authors and a statistician. Between-group comparisons will be performed by applying Student t-tests, Mann–Whitney U tests, Chi square tests or Fishers exact test, whichever is most appropriate. The primary analysis for primary and secondary outcomes will be based on an Intention-To-Treat (ITT) analysis comprise all study participants completed the baseline measurements. A generalized estimating equation (GEE) (Feng et al. 2001) approach will be taken, and the likelihood-based linear mixed effects repeated measures (LMERM) analyses (Mallinckrodt et al. 2001; Laird and Ware 1982) is the primary analysis. The LMERM-analysis includes the fixed variable *study treatment*, *visits* as factor variable, and *treatment*-*by*-*visits* interaction (intervention impact). The LMERM includes all available data at each time point and is the preferred methods of analysing clinical trial data in psychiatry due to the fact that likelihood approach deals with missing data in follow-ups assuming missingness is at random. Planned comparisons will be done with the LMERM models to determine between-group differences in score change from baseline to week 2, week 10, week 20 and week 24. Additional per-protocol analysis includes participants who completed the study intervention. Sensitivity analysis will evaluate missing at random assumptions for missing follow-up data. Missing data will be imputed assuming Missing Not At Random (MNAR) in intervention, control and both arms respectively and robustness of finding under different MNAR assumptions will be examined.

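### Seven days off tablets or a missed visit window is a reason to leave the study, with no later MADRS ratings provided for, so the ITT analysis does not observe the effect of assignment at week 20

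*Protocol article*

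**What the plan says.** The Discontinuation criteria (under Participant eligibility) open with "Participants will discontinue the study under the following circumstances". Two items in that list concern adherence and timing: "Discontinues study treatment for 7 or more consecutive days", and "Does not comply with the defined study visits (visits within 7 days prior or after the computer-generated date"). The list also holds withdrawal of consent and several safety or clinical reasons, such as "Becomes increasingly suicidal during the study as judged by investigator".

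Under Visits and telephone calls, the visits are "planned to be at week 2, 10, 20 and 24 (± 7 days for each visit"). Calls at weeks 6 and 15 serve adherence and adverse events; Table 1 lists no rating for them.

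The only follow-up described after an early exit is for safety: "Participants who discontinue study participation due to SAEs or SARs will be followed until the SAE/SAR has disappeared or the SAE/SAR is stable". The "4-weeks follow up after study treatment discontinuation" in Trial design is the week-24 visit, which comes after the scheduled 20 weeks of treatment.

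The Statistical analysis plan section makes ITT primary, in everyone with baseline measurements. It uses a linear mixed model (LMERM) with treatment, visit and their interaction, fitted to whatever ratings exist, on the ground that the "likelihood approach deals with missing data in follow-ups assuming missingness is at random". It adds MNAR imputation by arm and in both arms, and a per-protocol analysis of those who finished the treatment course. The sample size section assumes an 8-point difference with SD 10, a 40% drop-out rate and 78 recruited.

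**The concern.** An ITT analysis is meant to compare the arms as randomised, whatever happens to adherence. That needs outcomes from people who stopped their tablets or came late. Here the protocol turns both events into exits from the study, so it creates part of the missing data that the primary model must then handle by assumption.

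At stake is what the week-20 MADRS difference means. If those who stop lose some or all of the benefit, a model without their later ratings estimates something nearer the effect in people who kept taking tablets than the effect of being assigned to them. If exits follow worsening that no visit recorded, or differ between arms for reasons not seen in the data, the estimate can also be biased under its own assumption. Ratings not taken cannot be recovered at analysis.

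**Working it through.** **Step 1: the sections side by side.**

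- The discontinuation list names study treatment as the thing stopped (the trigger) and the study as the thing left (the consequence). The two are distinguished within the same list, so the plain reading is exit from the study.
- The week-20 visit falls on day 20 × 7 = 140, with a window of days 133 to 147. A participant who could be rated on day 150 is 3 days outside it and, read literally, meets the visit criterion.
- If the 7-day rule is applied, a participant with a week-20 MADRS has had no gap of 7 or more consecutive days. The observed week-20 data in the ITT model therefore come from almost the same people as the per-protocol set. The two analyses differ mainly through the earlier visits of those who left.
- MADRS is rated at weeks 2, 10 and 20, so the intervals between on-treatment ratings are 8 and 10 weeks. Worsening that begins and leads to an exit within such an interval need not appear in any recorded score, and missing at random covers only what was recorded.

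**Step 2: the plan's figures.** The recruitment target follows from 56 × 1.4 = 78.4, given as 78. With 40% of 78 leaving, 78 × 0.6 = 46.8, so about 47 have a week-20 rating and about 31 do not. (Whether 56 and 78 are the right sample sizes is a separate matter and does not affect this point.)

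**Step 3: possible size.** Let p be the share of participants who leave under these two rules, equal in both arms, and r the share of the 8-point benefit that they keep. Assume that the mixed model without their later ratings still targets 8 points.

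- Effect of assignment = 8 × [1 − p(1 − r)]
- Gap = 8 × p × (1 − r)

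| p | Effect of assignment, r = 0 | Gap, r = 0 | Gap, r = 0.5 |
|---|---|---|---|
| 10% | 7.2 | 0.8 | 0.4 |
| 20% | 6.4 | 1.6 | 0.8 |
| 40% | 4.8 | 3.2 | 1.6 |

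The documents give neither p nor r. The 40% row assigns the entire expected drop-out to the two rules and is an upper bound under the plan's own drop-out figure. Someone who leaves only because a visit was late may still be taking tablets; for that person r is near 1 and the gap near 0.

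**The case against.** **The article is condensed.** It never says that MADRS ratings cease; that is inferred from its wording about leaving the study and from the absence of any other provision. A fuller protocol might continue the ratings. This stands as a limit. It does not remove the point, because exit from the study is a stated rule here and not an omitted detail.

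**A single late visit.** A reader might infer that one visit outside the window is enough. The criterion refers to visits in the plural and gives no number. Its literal wording, with a window set for each visit, allows that reading but does not establish it.

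**Missing-data handling.** Ratings before exit are kept, and exit that depends on recorded MADRS is compatible with missing at random. A reader might infer that any outcome-related exit breaks the assumption; it does not. The MNAR analyses also address departures that differ by arm. These provisions soften the problem, but they vary assumptions about ratings that could have been taken.

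**What ITT means here.** The section defines ITT only as everyone with baseline measurements, so the gap in the table is a difference between two target effects. It is an error only if the result is presented as the effect of assignment, which is how an ITT label is normally read.

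**Power.** It is tempting to add that the rule costs power. That does not follow. By a two-sided t-test with SD 10 and 1:1 allocation (assumed), about 47 rated participants give 76.3% power for 8 points. With all 78 rated, power is 93.7% if the 40% who stop lose none of the effect (8.0 points), 79.7% if they lose half (6.4) and 55.3% if they lose all (4.8). Keeping people in may raise or lower power.

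**Clinical withdrawal rules.** Reasons such as suicidality or involuntary admission protect participants, and involuntary admission is also an exclusion criterion at entry. Those rules are not challenged here.

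**Conclusion.** The point holds for the adherence and visit-window triggers. As written, both take a participant out of the study, and nothing provides for MADRS ratings afterwards. The ITT mixed model then has week-20 data almost only from those who stayed on tablets and in the window, relies on missing at random for the rest, and does not observe the effect of assignment.

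The size is unknown. On the 8-point effect, the gap would be 0.8 or 1.6 points if 10% or 20% left under these rules and kept no benefit. A reader might infer from the 40% drop-out that the plan overstates the effect by 3.2 points. The documents do not support that: they do not split the 40% by cause, it would include withdrawals of consent that no rule change recovers, and they say nothing about benefit retained after stopping.

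The conclusion rests on reading the discontinuation list literally and on the article's silence about later ratings. It claims neither a gain in power nor that the missing-at-random assumption is known to fail.

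**What to change.** Reconcile the Discontinuation criteria with the Statistical analysis plan section:

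1. For 7 or more days off tablets and for visit-window non-compliance, separate stopping study medication from leaving the study.
2. Continue the scheduled ratings at weeks 2, 10, 20 and 24 for everyone in either group who still consents.
3. Accept ratings taken outside the window, recorded with their actual date.
4. Include off-treatment and late ratings in the ITT mixed model, and handle adherence and window deviations only in the per-protocol set.
5. Leave the safety and clinical withdrawal reasons (suicidality, involuntary admission, pregnancy, SAE/SAR) to the investigators. Ask only that the text say whether outcome ratings continue after each.

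The cost is a protocol amendment, consent wording and a few more ratings by the existing raters at visits already scheduled. The estimated effect may be smaller, because it would then include people who stopped.

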### Randomization

Participants will be randomized to NAC or placebo treatment by a computer-based random eight block number generator. The study participants will be randomised sequentially by the order they are enrolled into the trial. The randomization assignments will be hidden from the participants and the study investigators and raters. An independent pharmacy, Glostrup Pharmacy, will perform the randomization process, provide the randomization codes and the labelling of the tablet containers. The Coordinating Investigator ([name]) and Sponsor/Principal Investigator ([name]) will enrol and assign participants from two of the study centres, and the second Principal Investigator ([name]) and a project nurse ([name]) will enrol and assign participants from the latter study centre.

